#### Evaluation of Patients' Awareness of Their Disease

We will measure the patient's insight using the Scale to Assess Unawareness of Mental Disorders (SUMD) (43), which provides a broad assessment of the patients' thoughts and beliefs regarding their disease and medication. The Spanish adaptation of the SUMD is equivalent to the original, with similar reliability and external validity to those of the original version (44). The 9-item version will be used for this study.

#### Assessment of Prognosis

We will use the Strauss and Carpenter Prognostic Scale (45–47), an instrument that assesses the best status of the patient in the previous year in four areas: hospitalization, work, social activity, and global functioning. The scale is an interview-administered instrument with Likert-type response options ranging from 0 to 4; higher scores indicate a better prognosis. The scale was validated for schizophrenia studies in the Spanish population (48).

We will also assess the overall functioning of patients using the Spanish version of the GAF, which is recommended for Axis V disorders in the multiaxial system of DSM-IV-TR (49) and is based on the opinion of clinicians regarding the level of general activity and functioning of patients (severity). The scale was validated in patients with severe mental disorders (50).

In addition, the level of functioning will also be measured using the Children's Global Assessment Scale (C-GAS) (51, 52). GAF or C-GAS will be selected according to the patient's age.

#### Assessment of Adherence to Treatment

We will measure this variable using the Morisky Medication Adherence Scale (53), which has been validated for the Spanish population (54). It has four questions and assesses the attitudes of the patients toward their treatment. Patients with a score of four will be considered as having “good” adherence, while those with a score between 0 and three will be classified as having “poor” adherence.

#### Assessment of Drug Use

The use of drugs will be determined using the Addition Severity Index (55), which was adapted for the Spanish population by Guerra in 1992 (56) and evaluates substance abuse problems. It is a semi-structured interview with 142 items. Data correspond to the last 30 days in both objective and subjective reports.

#### Assessment of Quality of Life

Quality of life will be assessed using the World Health Organization Quality of Life WHOQOL-BREF Questionnaire (57). The short version is composed of 26 items exploring 4 dimensions (physical health, psychological health, social relationships, and the environment). Spanish trials were the first to report on the validity of the WHOQOL in people with schizophrenia (58).

Quality of life will also be assessed using the EuroQoL questionnaire (59), which measures five dimensions (mobility, self-care, usual activities, pain/discomfort, and anxiety/depression). It also contains a visual analog scale represented by a vertical line on which subjects rate their self-perceived health status from 0 (the worst) to 100 (the best imaginable health status). The validated Spanish version of this scale is simple and practical (60).

### Data Management

Data confidentiality will be ensured using a coded database. In order to further guarantee confidentiality, access will be restricted to the therapist and the investigators. All data will be anonymous and confidential and will have a code. All the documents recorded to collect data will be saved and filed following the regulations in force in Spain (*General Regulation on Data Protection in force in 2018*).

### Software Development

We will develop an Android Mobile app with a web support and administration application and a cloud-based backend database, which will register fine-grain interactions between the users and the app in order to generate relevant granular data and key performance indicators and thus support a wide range of further analyses.

The application will be designed and developed using software engineering–based Agile Methodologies under SCRUM principles (empiric control of the development process using continuous feedback procedures). The whole mobile app functionality and its user interfaces and interactions will be designed under the premise of maximizing the user experience in order to boost adherence to treatment.

All of the communications between the mobile app and the supporting backend will be protected by means of an SSL digital certificate on the server, which will provide end-to-end encrypted communications.

#### Software: Control of Adherence to the App

The software used in the study is based on a technology that reports the access and time that a person been in the app. The app also has a reminders and warnings that will guarantee that patients can use it and not discontinue treatment.

### Intervention Programme

Before designing the mobile app, a focus group with young people with psychosis was carried out at the Child and Adolescent Psychiatry Department, Gregorio Marañon Hospital. The opinions and contributions of the participants on the design of the modules were very useful for the design of the mobile app.

#### Mobile Phone Psychotherapy App

The psychotherapy app programme is composed of five modules:
-Psychoeducational module-Module on recognition of symptoms and prevention of relapses-Problem-solving module-Mindfulness module-Contact wall module

The modules will be assessed in parallel throughout the study. Each module is described in detail below.

##### Psychoeducational Module

The psychoeducational module focuses on improving patients' insight into their illness, adherence, detection and identification of prodromes, early intervention to prevent relapses, healthy lifestyles and techniques for managing anxiety, social skills, and consumption of toxic substances. In order to facilitate integration, psychoeducation will be administered through animated videos (comic-like format) of about 2–3 min in duration, which were made and edited by clinical experts in psychosis.

The 12 sessions are included in module are in Table 1.

**Table 1 T1:** Online sessions of the psychoeducation module.

**Number of session**	**Title**
1.	What is a first episode of psychosis? Protective and risk factors
2.	Recognition of symptoms (positive, negative, and affective)
3.	Treatment (types and adherence)
4.	Treatment (adverse effects)
5.	Drugs and psychosis
6.	Prevention of relapses: Protective and risk factors
7.	How to act in a crisis
8.	Healthy lifestyle I: Stress
9.	Healthy lifestyle II: Protective factors in psychosis
10.	Social skills: Communication and assertiveness techniques
11.	Adolescence
12.	New technologies

All of the selected sessions are based on previous studies of that have shown the efficacy of psychoeducational interventions in adolescents with FEP (61–64).

The program will automatically check whether the video has been watched. In addition, it will be accompanied by a 5-item questionnaire about each video to guarantee that the patient has understood the content.

##### Module on Recognition of Symptoms and Prevention of Relapses: Alert System

This module will add some important novelties. It has an alert system by which patients will be able to check their symptoms, cognitive performance, and emotional and behavioral circumstances *weekly*. The system will return feedback with specific recommendations. This module is based on previous studies that have shown efficacy for FEP patients (20, 21). For example, if a patient begins to spend more time at home, becomes more isolated, and complains of having less energy, the system, automatically, will send recommendations to the patient via the mobile app. Some of the recommendations could be as follows: “We feel that you are changing your habits, it seems you are more inactive. We recommend you to try to go for a walk, even around the area of your house; to try not to get into bed and try to do some activities that you liked before. If you need to talk to a friend or family member to encourage you and accompany you to prevent the situation from becoming worse, please do so. Nevertheless, we recommend you to talk with your psychiatrist or psychologist to see what is happening.” This system, for example, also gives recommendations for visiting the psychiatrist or psychologist or for hygiene activities.

##### Problem-Solving Module

> In this module, the participants can share their problems and ask other participants to provide possible solutions. All participants have access to a problem-solving wall. The module is based on McFarlane's Multiple Family therapy model and on the application of problem-solving techniques that have proven efficacious for patients with severe mental disorders and their relatives (8, 61–64). A moderator (psychologist or psychiatrist specialized in FEP) will review the contents of the forum and lead participants to relevant topics if necessary.

##### Mindfulness Module

> In this module, we will explain the concept of mindfulness and its objectives with a 3-min video. The module consists of 3 recordings made by clinicians who are experts in mindfulness, in which three techniques of this type of therapy are developed. The module will be taught by means of audio recordings in which the techniques described will be body scan and attention focusing (breathing and breathing) to feel better (self-compassion). The aim of the module is to help to reduce anxiety and to increase the sensation of control. This type of intervention has demonstrated efficacy with psychosis (21, 65), even when administered via mobile technology (66).

##### Contact Wall Module

The contact wall module will include a contact wall based on previous studies that have shown efficacy in FEP (20). Moreover, a review about this strategy concluded that a contact wall can improve social contact and reduce isolation in patients with psychosis (67). Patients can use the wall to share their interests and experiences. The module can help to develop sociability and will bring a sense of normality, favoring activities according to age and preferences. It does not necessarily focus on the disease. The contact wall aims to act as a social space, within the app, where patients can exchange information on their leisure interests. Information published on the contact wall is supervised and previously approved by a therapist, who acts as a moderator.

#### Treatment As Usual (TAU)

Treatment as usual refers to the standard treatment provided in the Spanish National Health Service. For patients with FEP, this consists of ambulatory psychopharmacotherapy and regular sessions with an assigned psychiatrist. In some cases, it involves outpatient treatment with a clinical psychologist, thus enabling patients to manage their condition themselves.

## Anticipant Results

The study anticipates that adolescent patients with psychosis of the experimental group, after the application of the mobile app intervention, will improve, significantly, their symptoms, adherence, awareness, prognosis and quality of life and will reduce the drugs consumption, compared with the control group. The study hypothesis is that the online treatment will be more effective than the treatment as usual intervention in reducing the indicated variables.

## Statistical Analysis

Data will be analyzed on an intention-to-treat (ITT) basis (68). In accordance with the ITT principle, all patients will be included in the analysis, independently of the groups to which they are randomly assigned and regardless of whether they complete the treatment or not.

Outcomes will be reported with 95% confidence intervals. All data will be analyzed using SPSS version 21.0. The level of bilateral significance for all statistical tests will be established at α = 0.05.

The baseline characteristics of the sample will be compared between the two groups using the Pearson chi square test for the categorical variables and the *t* test or Mann-Whitney test for the quantitative variables.

Mixed model repeated-measures analysis will be used to explore the following effects: group × time interaction between the control group and the intervention group for clinical and functional variables during the follow-up period. Intergroup and intragroup differences during follow-up will also be studied.

The effect sizes will be calculated to quantify the effect of the intervention on the groups. To consider a certain value a large or small effect size, the following orientations will be accepted: *d* = 0.20 (small), *d* = 0.50 (moderate), and *d* = 0.80 (large) (69).

The research results will be reported in agreement with the Consolidated Standards of Reporting Trials (CONSORT) 2010 statements (70, 71) and the Standard Protocol Item: Recommendations for Interventional Trials (SPIRIT) guidelines (72, 73).

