## Abstract

**Introduction:** Previous studies have shown an improvement in the access to treatment for patients with first-episode psychosis (FEP), specifically young patients, through mobile app–based interventions. The aim of this study is to test the effectiveness of a mobile app–based intervention to improve community functioning in adolescents with FEP. Mobile app–based interventions could increase quality of life and disease awareness, which improve adherence to treatment and reduce the frequency of relapses and rehospitalizations in adolescents with FEP.

**Methods:** This article describes a mobile app treatment and the pilot trial protocol for patients with FEP. We will perform a single-blind randomized clinical trial (RCT) including patients with FEP aged 14–19 years recruited from Gregorio Marañón Hospital, Madrid, Spain. Patients will be randomly assigned to an intervention group, which will receive treatment as usual plus five modules of a psychological intervention through the mobile app (psychoeducation, recognition of symptoms and prevention of relapses, problem solving, mindfulness, and contact wall), or to a control group (standard care). The effectiveness of the intervention will be assessed by means of an extensive battery of clinical tests at baseline and at 3 months of follow-up. The primary outcome is reduction in psychotic and depressive symptoms; secondary outcomes comprise adherence, awareness, use of drugs, and quality of life. Data will be analyzed on an intention-to-treat (ITT) basis. Mixed model repeated-measures analysis will be used to explore the following effect: group × time interaction between the control group and the intervention group for clinical and functional variables during the follow-up period.

**Discussion:** This is an innovative study for the assessment of a psychological intervention through a mobile app for patients with FEP during the critical period. This pilot RCT is intended to be a precursor to larger studies, which in turn could facilitate dissemination of mobile app therapy for patients with FEP.

**Ethics and Dissemination:** The local ethics committee approved the study protocol. All participants must sign the informed consent, to participate. After finalizing the study, the results will be published.

**Trial registration:** NCT03161249. NCT clinicaltrials.gov. Date of registration in primary registry 02 May 2017. clinicaltrials.gov.

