### Sample Size Calculation

Few previous longitudinal studies have analyzed children and adolescents with the characteristics of the patients in the present study (26, 27). Sample size was calculated based on data published in the literature related to the main issue addressed in the study (28), namely, mu1 (42.5) and mu2 (31.9), sigma value (11.54), value for α (0.05), and value for desired power (0.80). The proposed sample size was 50 patients-−25 per group—which is anticipated to be further reduced by loss to follow-up, resulting in an approximate final sample of 38–42 patients. In order to obtain a power of 80% to detect differences from the null hypothesis, H0: μ1 = μ2, using inferences to compare the means of two independent samples, with a significance level of 5%, we need to include at least 19 patients in the experimental group and 19 patients in the control group. Recruitment of participants is adjusted to 25 per group to account for possible dropouts.

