#### Evaluation of Patients' Symptoms

Psychotic symptoms will be assessed using the Positive and Negative Syndrome Scale PANSS (32), which is composed of 30 items covering positive and negative symptoms and the general psychopathology of the disorder. Each item is measured using a 7-point Likert scale reflecting the severity of symptoms from 1 (none) to 7 (extreme symptoms). The scale has been validated for the Spanish population (33). In addition, Positive symptoms will be assessed using SAPS (34) and negative symptoms using SANS (35), both of which were validated in Spanish by Vazquez in 1989 (36, 37). SAPS has 34 items and SANS 25. Both have good psychometric properties.

Trait and state anxiety will be measured using the State-Trait Anxiety Inventory (STAI) (38). This instrument has two parts: one that assesses the anxiety experienced by patients during the previous week (namely “state”) using 20 items with 4 response options; and another that assesses their usual reactions to specific situations (namely “trait anxiety”), also using 20 items with 4 response options. The STAI was adapted from the Spanish study in 1978 by Bermudez (39), who found that in these items, the mean and the reliability (Cronbach alpha and test-retest correlation) were similar to those of the original version (40).

Mood symptoms will be evaluated using the Hamilton Rating Scale for Depression (HRSD) (41) validated for the Spanish population (42). This instrument is in three different versions (5, 7, 21 items) and has good psychometric properties. The 21-item version will be used for this study.

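### The primary outcome joins two symptom constructs with no primary score and no success rule, while every test is set at 0.05; depending on the rule, either the 5% error rate or the 80% power is not met

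*Protocol article*

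**What the plan says.** The Abstract of the protocol article defines the endpoint: "The primary outcome is reduction in psychotic and depressive symptoms". Adherence, awareness, drug use and quality of life are secondary.

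The section on evaluation of patients' symptoms gives the instruments. "Psychotic symptoms will be assessed using the Positive and Negative Syndrome Scale PANSS". It continues: "In addition, Positive symptoms will be assessed using SAPS", with SANS for negative symptoms. For mood it uses the 21-item HRSD. It does not rank these scales or say which score carries the primary outcome.

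Under Statistical Analysis the model is general: "Mixed model repeated-measures analysis will be used to explore the following effects: group × time interaction between the control group and the intervention group", applied to the clinical and functional variables as a group. The significance level is set once for everything: "The level of bilateral significance for all statistical tests will be established at α = 0.05".

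The Sample Size Calculation rests on one comparison of two means: "namely, mu1 (42.5) and mu2 (31.9), sigma value (11.54), value for α (0.05), and value for desired power (0.80". It does not name the scale behind the means, and it arrives at 19 per group, raised to 25 for dropout, with 38–42 patients expected at the end.

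**The concern.** A two-part primary outcome needs a rule for success: either part, both parts, or one designated part. The article gives none, and it offers three scales for one of the two parts. The level is nevertheless fixed at 0.05 for each test, so this is more than a detail left unsaid. An analysis plan that split alpha would depart from the published sentence.

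The rule matters in both directions. If either construct is enough, several tests at 0.05 feed one claim and its error rate exceeds 5%. If both are needed, the error rate is safe, but a sample sized for a single comparison is too small for 80% power on the joint claim. With no score named, the primary result could also be chosen after the data are seen.

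**Working it through.** **Inputs.** From the Sample Size Calculation: means 42.5 and 31.9 (difference 10.6), SD 11.54, two-sided α 0.05, power 0.80, 19 per group, 38–42 patients at the end (19–21 per group). From the symptom section: two constructs and four scales. The article gives no correlations between scales, so those below are assumptions.

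**1. The plan's own figure.** n = 2 × [11.54 × (1.960 + 0.842) / 10.6]² = 18.6, rounded up to 19 per group. The stated 19 reproduces for one two-sided test. The standardised effect is 10.6 / 11.54 = 0.919. Power at 19 per group is 80.8% by normal approximation and 78.7% by noncentral t.

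**2. Rule A: one significant result is enough.** For k independent tests at 0.05 the error rate is 1 − 0.95^k, which gives 1 − 0.95² = 9.75% for two and 1 − 0.95⁴ = 18.5% for four. Equally correlated two-sided z tests (simulation, 2 million draws) give:

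| Assumed correlation | Two tests (PANSS, HRSD) | Four tests (plus SAPS, SANS) |
|---|---|---|
| 0 | 9.8% | 18.5% |
| 0.5 | 9.1% | 15.6% |
| 0.7 | 8.3% | 13.0% |

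A mixed pattern for the four scales (correlations 0.3 to 0.7, higher between PANSS and SAPS or SANS) gives about 15%.

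**3. Rule B: both constructs must be significant, one score each.** The claim is false if either null holds, and that null is rejected at most 5% of the time, so the error rate is at most 5% with no adjustment. Joint power at 19 per group, with the planned effect on both scores, is 0.808² = 65% by normal approximation if the tests are independent, and about 72% at correlation 0.7. By noncentral t the independent case is 0.787² = 62%, and about 70% at 0.7. At 21 per group the independent normal figure is 0.845² = 71%.

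**4. Rule C: HRSD plus any one of the three psychosis scales.** In the worst case HRSD has a real effect and is nearly sure to be significant, so the error is that of three tests: 1 − 0.95³ = 14.3% if independent, 10.9% at correlation 0.7.

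**5. Power for one endpoint if alpha is split over two scores (noncentral t).**

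| Per group | α = 0.05 | α = 0.025 |
|---|---|---|
| 19 | 78.7% | 68.8% |
| 21 | 82.7% | 73.9% |

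**The case against.** The strongest reply is that the article's wording is conjunctive. It speaks of psychotic and depressive symptoms together, and the hypotheses list the outcomes jointly. Read as requiring both on one score each, the type I error is controlled. This stands, and for that reason the error rate cannot be called inflated outright. It does not rescue the power, because the sample was sized for one comparison.

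A reader might infer that the false-positive rate is 8–19% as a matter of fact. The article does not support that. With no success rule the rate is undetermined, and the range applies only if any one result suffices. The 19% end also needs four independent scales, which is not credible: by the article's own description PANSS covers positive and negative symptoms, which SAPS and SANS measure again in the same patients.

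It can also be said that the symptom section ties psychotic symptoms to PANSS and adds SAPS and SANS as further measures. PANSS and HRSD is then the natural reading, with 8–10% under the either-construct rule. That is fair, but the text does not make it a rule, and it still leaves open which PANSS score is meant.

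The study is called a pilot, the model is said to explore effects, and confidence intervals and effect sizes will be reported. This lowers the severity. It does not remove the point: the Aims speak of evaluating efficacy, the Anticipant Results section expects significant improvement over control, and the trial is powered at 80%.

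Finally, a full protocol or analysis plan may name the score and the rule. That limits the criticism to what is printed: a two-part primary outcome together with one fixed level for every test.

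**Conclusion.** The point holds in conditional form and should be fixed; it is not a fatal flaw. The error rate for the primary claim depends on a rule that the article does not state.

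- Either construct suffices, PANSS and HRSD: about 8–10%.
- Any of the four scales suffices: about 13–16%.
- Both must succeed, one score each: at most 5%, but with joint power at 19 per group of about 65–72% (normal approximation) or about 62% (noncentral t, independent tests).

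Under each of these rules, the 5% or the 80% is not delivered. The figures rest on assumed correlations (0 to 0.7 for two scales, 0.5 to 0.7 for four). The power figures also assume that the planned effect, taken from an unnamed scale, holds on both constructs.

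**What to change.** Before any outcome data are seen:

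1. Name one 3-month score per construct: one specified PANSS score and the HRSD-21 total.
2. Choose and state one rule: control the overall two-sided 5% over the two scores with Holm; or name one of them as the single primary; or require both and restate the joint power.
3. Make SAPS, SANS and all other scales secondary, reported as estimates with 95% confidence intervals and without confirmatory claims.
4. Limit the sentence that sets 0.05 for all tests to match.
5. Reconcile the choice with the Abstract and Introduction, which give improved community functioning as the aim, while the primary outcome is symptoms.

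The change is one of wording. The cost depends on the rule. Under Holm, noncentral-t power for one endpoint at the first step (0.025) is about 69% at 19 per group and 74% at 21, against 79% and 83% at 0.05. Under the both-must-succeed rule the cost is the lower joint power given above. A single primary costs no power, but the other construct then carries no confirmatory claim.

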### Patients' Recruitment

We will recruit patients from the Child and Adolescent Psychiatry Department of Hospital General Universitario Gregorio Marañón in Madrid, Spain between 2018 and 2019. Recruitment will begin after the protocol has been published. Patients who agree to participate in the study will be assessed and randomly assigned to the intervention group (mobile app intervention) or to the control group (standard care). The intervention group will receive treatment as usual plus a psychological intervention through a mobile app. The control group will receive only the treatment as usual (pharmacotherapy together with regular sessions with a psychiatrist and/or clinical psychologist). The pharmacological treatment will be that prescribed by the patient's psychiatrist.

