### Clinical Assessment Criteria

Data on the major clinical and demographic variables will be entered on a data collection form. All patients will be assessed by blind raters at baseline and at 3 months after inclusion in the study, after signature of informed consent, and randomization. During follow-up, patients who use the app will be “monitored” by mental health professionals. Their reference clinicians will fully informed, and families will know that the adolescents are participating in the study. Any emergency or major side effect in either of the study arms will be pointed out, and the patient will be removed from the study. If necessary, the patient will be referred to the emergency department.

All the instruments used in the study have appropriate psychometric properties (29–31).

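### With only two visits, the planned group × time interaction is in effect a comparison of mean change: valid, but less precise than adjusting for baseline

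*Protocol article*

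**What the plan says.** The Statistical Analysis section names one model, a repeated-measures mixed model, and one effect: the "group × time interaction between the control group and the intervention group for clinical and functional variables during the follow-up period". It adds that differences between and within groups will be studied, and that effect sizes will be computed. It mentions neither a baseline covariate nor a constraint that the arms share a common baseline mean.

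Clinical Assessment Criteria fixes the visits: "All patients will be assessed by blind raters at baseline and at 3 months after inclusion in the study". There is no other assessment.

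Sample Size Calculation rests on a different comparison, of two independent means, with means 42.5 and 31.9, SD 11.54, α 0.05 and power 0.80. It requires 19 per group, recruits 25 per group and expects 38–42 patients to remain. Tests are two-sided: "The level of bilateral significance for all statistical tests will be established at α = 0.05".

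**The concern.** With one post-baseline visit, a time factor can exist only if baseline is itself one of the response values. A model with group, time and their interaction, and with baseline means free to differ by arm, then estimates the difference in mean change. It spends information on estimating a baseline difference that randomisation has already set to zero in expectation. Adjusting the 3-month value for baseline uses that knowledge and has smaller variance.

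What is at stake is precision in a small trial. The article expects about 40 completers and lists the small number of patients as a limitation. When r is below 0.5, the completers' change score is noisier even than the unadjusted 3-month comparison used for sizing.

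**Working it through.** **Inputs from the article.** Difference 42.5 − 31.9 = 10.6; SD s = 11.54; two-sided α = 0.05; 25 randomised and at least 19 evaluable per arm.

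**Assumptions, not in the article.** r = 0.3, 0.5 or 0.7; 10.6 is the treatment effect at 3 months; s is the SD at both visits; dropout is completely at random.

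**Step 1: the plan's own figure.** n per arm = 2 × (11.54 × (1.960 + 0.842)/10.6)² = 18.6, so 19. The stated size reproduces. Power at 19 per arm is 80.8% by the normal approximation and 78.7% by the exact t-test.

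**Step 2: identity of the contrasts.** On simulated complete two-visit data (19 per arm), the interaction coefficient from a random-intercept model was −12.153 (SE 3.127). The difference in mean change was −12.153 (SE 3.127).

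**Step 3: variance with complete data.** Per patient, the change score has variance 2(1 − r)s² and the baseline-adjusted value (1 − r²)s². The ratio is 2(1 − r)/(1 − r²) = 2/(1 + r).

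**Step 4: variance with the expected dropout.** With N = 25 baselines and m = 19 completers per arm, the unconstrained mixed model also uses the dropouts' baselines. Its variance per arm is s²[(1 − r²)/m + (1 − r)²/N], against s²(1 − r²)/m for ANCOVA. The ratio is 1 + (m/N)(1 − r)/(1 + r), with m/N = 0.76. At r = 0.3, for example, it is 1 + 0.76 × 0.7/1.3 = 1.41.

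**Step 5: power.** Noncentral t, with SE equal to the square root of twice the per-arm variance of the estimate.

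| | r = 0.3 | r = 0.5 | r = 0.7 |
|---|---|---|---|
| Variance ratio to ANCOVA, completers only | 1.54 | 1.33 | 1.18 |
| Variance ratio, dropouts' baselines used | 1.41 | 1.25 | 1.13 |
| SE, change score in completers | 4.43 | 3.74 | 2.90 |
| SE, unconstrained mixed model | 4.24 | 3.63 | 2.85 |
| SE, ANCOVA | 3.57 | 3.24 | 2.67 |
| Power, change score | 64% | 79% | 94% |
| Power, unconstrained mixed model | 68% | 81% | 95% |
| Power, ANCOVA | 82% | 89% | 97% |

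**Step 6: cost of adjustment.** Estimating the baseline slope inflates ANCOVA's variance by about 1/34, or 3%, at 38 patients. Counting this, ANCOVA's power is 81%, 88% and 97%. A simulation of 25 randomised and 19 completing per arm, which includes this cost, gave SEs of 4.21, 3.66 and 2.87 for the mixed model and 3.61, 3.31 and 2.72 for ANCOVA. Those are variance ratios of about 1.36, 1.22 and 1.11. Against the completers' change score, adjustment stops paying only when (1 + r)/2 × 35/34 exceeds 1, that is, when r exceeds about 0.94.

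**Step 7: sample size.** For 80% power by the normal approximation, the change score needs 27, 19 and 12 completers per arm, against 17, 14 and 10 with adjustment.

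**The case against.** The article does not write out its model. A mixed model with baseline means constrained equal also carries its treatment effect in a group × time term, so the quoted words could describe the better analysis, and an unseen analysis plan may say so. It is true that the unconstrained form is an inference. It is nevertheless the ordinary reading of a group × time interaction with nothing further stated. The article also commits to that contrast rather than leaving it open, so the baseline handling should be stated.

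The change-score figures overstate the loss once dropouts' baselines enter the model. That stands, and the smaller ratios are given above. The size also depends on r, which is assumed.

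Some stronger readings are tempting but not supported:

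- **Bias or invalidity.** A reader might infer that chance baseline imbalance biases the interaction. It does not: over randomisations the estimate is unbiased and the test valid, and the imbalance is already reflected in the standard error.
- **A baseline taken after allocation.** Clinical Assessment Criteria places assessments "at baseline and at 3 months after inclusion in the study, after signature of informed consent, and randomization", which could be read that way. The last phrase is loose and may attach to inclusion or to the 3-month visit. Patients' Recruitment says patients "will be assessed and randomly assigned to the intervention group", which puts assessment first, and the flow diagram is not available here. This is an ambiguity of wording, not evidence of a contaminated baseline.
- **Baseline tests and effect sizes.** The plan says "The baseline characteristics of the sample will be compared between the two groups using the Pearson chi square test" (and other tests for quantitative variables). It gives these tests no role in adjustment, so objecting to them is a reporting preference. Nor does it say that the effect size will come from within-group change.

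Finally, this is a pilot, and the model is said to explore effects. That limits the consequences, but a more precise estimate serves a pilot equally well.

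**Conclusion.** The point holds as a weakness in efficiency, not as an error. On the ordinary reading, the planned contrast has a variance about 1.4, 1.25 or 1.1 times that of baseline adjustment at r = 0.3, 0.5 or 0.7 with the expected dropout, and up to 1.54, 1.33 or 1.18 times in completers alone. The conclusion that adjustment is more precise does not depend on the exact r unless r is very high, but the size of the gain does, and it is small above about 0.8.

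It would go too far to conclude that the trial is underpowered by this choice. At r = 0.5 the contrast roughly matches the power used for sizing, and at 0.7 it exceeds it. Only below about 0.5 do 19 completers per arm fall clearly short of 80%. All power figures rest on taking 10.6 as the treatment effect and 11.54 as the SD at both visits.

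**What to change.** For each quantitative outcome, state that the primary estimate is the 3-month between-group difference adjusted for the baseline score, with its 95% confidence interval. Either of two models will do:

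- ANCOVA of the 3-month score on group and baseline score; or
- the same mixed model with baseline means constrained equal across arms. This keeps patients who miss a visit and so fits the intention-to-treat aim.

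State that the reported effect size is derived from this between-group difference.

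As a minor wording point, reconcile Patients' Recruitment with Clinical Assessment Criteria so that baseline assessment clearly precedes randomisation.

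The cost is one paragraph of analysis text and one clarifying sentence. No extra patients, visits or data are needed. The statistical price is about 3% of variance at 38 patients.
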